## 1. Purpose of the Study and Background

### 1.1. Background

The US is in the midst of an opioid crisis that is having an unprecedented impact on population health. Individuals with opioid use disorder (OUD) have disproportionately high rates of hospitalization, and low rates of addiction treatment. Hospitalization presents an opportunity to engage this population in effective treatment, thereby reducing their risk of acute care utilization, overdose (OD) death, and poor health and social outcomes, and yet in most hospitals OUD is not addressed. Addiction consult models offer a potential solution, by using multidisciplinary teams to evaluate patients, start addiction treatment in the hospital, and connect patients to post-discharge care.

A *Consult for Addiction Treatment and Care in Hospitals (CATCH)* intervention is being introduced into the New York City Health and Hospitals (H+H) system. H+H is the largest municipal hospital system in the US, and its 70 locations throughout the five boroughs of NYC provide care to over one million New Yorkers each year. In 2018, CATCH will be implemented in six H+H hospitals, with the intention to spread these services throughout the H+H system. CATCH Teams will evaluate hospital inpatients to diagnose OUD, start medication for addiction treatment (MAT) when indicated, and directly link patients to post-discharge treatment.

### 1.2. Brief overview

This pragmatic clinical trial seeks to evaluate the effectiveness of the CATCH intervention as a strategy for engaging patients with OUD in addiction treatment. The CATCH intervention uses a multidisciplinary addiction consult team, working in the hospital inpatient setting, to evaluate patients with substance use disorders (SUD), start MAT while patients are hospitalized, and connect patients to post-discharge treatment. Beginning in 2018, CATCH will be implemented in six NYC H+H hospitals; this study takes advantage of the rollout of the intervention to study the effectiveness and implementation of CATCH as delivered by clinical staff and at scale.

The study sites are the 6 hospitals that have been selected by H+H for implementing CATCH services. A stepped-wedge cluster randomized trial design will determine the impact of CATCH on opioid treatment outcomes in comparison to usual care for an approximately 12-28 month control period, followed by an approximately 12-41 month intervention period, at each site. Consistent with a pragmatic trial approach, the research is conducted in collaboration with the health system, in real-world settings and at scale. The design applies random sequential assignment of sites to CATCH until all sites have converted, and utilizes existing administrative data to evaluate outcomes. This hybrid effectiveness-implementation study (Type 1) focuses primarily on the effectiveness of this new intervention for increasing initiation and engagement in treatment, while also measuring implementation outcomes to inform its later dissemination to other health systems. Using the RE-AIM framework, we will evaluate CATCH on dimensions that define its potential for public health impact.

### 1.3. Specific aims

The study has one primary and three secondary aims:

**Aim 1** (Primary aim): Evaluate the effectiveness of CATCH in increasing MAT initiation and engagement among patients with OUD. CATCH will start MAT while patients are hospitalized, but because meaningful outcomes require linking patients to ongoing care, our measures are based on receipt of post-discharge MAT.

Hypothesis 1a (H1a): Patients hospitalized during the CATCH period will have higher rates of treatment initiation, defined as initiating MAT outpatient treatment within 14 days of discharge.

Hypothesis 1b (H1b): Patients hospitalized during the CATCH period will have higher rates of treatment engagement, defined as having 2 or more additional MAT services within 30 days of treatment initiation.

**Aim 2:** Assess the effectiveness of CATCH for increasing MAT retention in patients with OUD. Hypothesis 2 (H2): Patients hospitalized during the CATCH period are more likely to be continuously retained in treatment for at least 6 months, in comparison to patients hospitalized during the usual care period,.

**Aim 3:** Compare the frequency of acute and ambulatory care utilization and overdose deaths, and their associated costs, among patients with OUD hospitalized during the CATCH period versus usual care, and assess the economic value of CATCH with respect to MAT initiation and retention. Hypotheses: Patients in the CATCH period will have (H3a) lower rates of ED and hospital admission, and (H3b) lower rates of overdose death, in the 12 months following the index hospitalization

**Aim 4:** Evaluate implementation outcomes at CATCH sites using a mixed methods approach to assess additional RE-AIM elements: *Reach* – proportion of eligible patients reached by CATCH; *Adoption* – utilization of CATCH by medical staff; *Implementation fidelity* – characteristics of the intervention as delivered to the target population. A mixed-methods approach, guided by the Consolidated Framework for Implementation Research (CFIR) and gathering data from patients and staff, will provide insights into barriers and facilitators of full-scale implementation.

#### 1.4. Study design

A stepped-wedge cluster randomized trial design will determine the impact of CATCH on OUD treatment outcomes in comparison to usual care, at each site. The design applies random sequential assignment of sites to CATCH until all six sites have converted, and primarily utilizes administrative data, (including Medicaid claims and electronic health record data), to evaluate outcomes. Interviews with CATCH staff and patients are included to inform implementation outcomes.

This is a Hybrid Type 1 study in which the primary focus is on the effectiveness of the CATCH intervention, but implementation process measures are also tracked. Distinct from pure effectiveness trials, hybrid studies aim to also answer the question “What are the barriers and facilitators to ‘real-world’ implementation of the intervention?” Hybrid Type 1 designs are appropriate when there is strong face validity and at least indirect evidence supporting the intervention, and it is associated with minimal risk. While a small RCT and multiple observational studies indicate that addiction medicine consult teams may be effective for increasing OUD treatment, many questions remain before this approach can be recommended for broad dissemination. This research will provide the required knowledge about effectiveness, while simultaneously collecting important information on the cost and feasibility of implementation.

Following our stepped-wedge randomized trial design, all sites are evaluated pre- and post-implementation, with start dates randomly assigned to improve causal inference. Each of the 6 participating hospitals will be randomly assigned to one of 6 start times; start times are separated by approximately 3 months. Each site has an approximately 12-28 month TAU observation period, followed by an approximately 12 to 41-month CATCH intervention period; the duration of TAU and CATCH periods are dependent on the site’s start time. Our main study outcomes are measured at 6 and 12 months following introduction of CATCH at each site, but administrative data will continue to be collected at all sites until the end of the study period (in the 14th Quarter of the study), thus allowing us to monitor the maintenance of outcomes. The primary outcome is the rate of MAT initiation and engagement following hospital discharge, measured in Medicaid claims data.

Figure 1. Stepped-wedge design with 6 sites

| Group  | Study Period |    |    |    |    |    |    |    |    |     |     |     |     |     |
|--------|--------------|----|----|----|----|----|----|----|----|-----|-----|-----|-----|-----|
|        | Q1           | Q2 | Q3 | Q4 | Q5 | Q6 | Q7 | Q8 | Q9 | Q10 | Q11 | Q12 | Q13 | Q14 |
| Site 1 |              |    |    |    |    |    |    |    |    |     |     |     |     |     |
| Site 2 |              |    |    |    |    |    |    |    |    |     |     |     |     |     |
| Site 3 |              |    |    |    |    |    |    |    |    |     |     |     |     |     |
| Site 4 |              |    |    |    |    |    |    |    |    |     |     |     |     |     |
| Site 5 |              |    |    |    |    |    |    |    |    |     |     |     |     |     |
| Site 6 |              |    |    |    |    |    |    |    |    |     |     |     |     |     |

**Legend:** Each box represents 3 mos [figure not shown] =Treatment as usual measures [figure not shown] =CATCH intervention measures

## 6. Woodhull Medical and Mental Health Center ([name])

### 1.6. Evaluation framework

Our study compares the impact of the CATCH intervention versus TAU on OUD treatment initiation, engagement, and retention, while assessing its adoption and implementation in practice. The assessment plan is organized by the RE-AIM

[figure not shown]

framework, which is one of the most widely applied frameworks for evaluating health behavior change programs. RE-AIM is appropriate for a pragmatic trial because it offers a framework for measuring the impact of an intervention *as delivered in real world environments*. Assessment of the five domains of RE-AIM provides an evaluation of a program's potential public health impact. In our study, **Effectiveness** is the rate of OUD treatment initiation and engagement (primary outcome). **Reach** is the proportion of patients who receive CATCH services. The product of Reach\*Effectiveness signifies the individual-level impact of the intervention. Implementation outcomes, measured in the intervention condition only, include: **Adoption**-the utilization of the CATCH teams by clinical staff, as measured by the rate of referrals of patients with OUD; and **Implementation fidelity**- the ability of the CATCH teams to identify and reach their target population, and deliver high-quality MAT. We have limited ability to study **Maintenance** in the time-limited context of this study, but the stepped-wedge design will allow us to measure Reach and Effectiveness for up to approximately 41 months following implementation of the CATCH intervention.

While the overarching framework guiding our evaluation is based on RE-AIM, we will use mixed methods to explore in-depth the organizational (organizational readiness, culture, priorities), individual (attitudes, norms), and intervention characteristics (complexity, relative advantage) of CATCH, as defined by the Consolidated Framework for Implementation Science (CFIR). These measures provide additional insights into the fidelity of the intervention as delivered, potential barriers and facilitators of its full-scale implementation, and behavioral and structural factors that may explain its effectiveness.

### 1.7. Primary and secondary outcome measures

Outcome measures are specified in Table 1. The primary outcomes, addressed in Aim 1, are MAT initiation and engagement. Treatment initiation is defined as having an outpatient MAT encounter (in a MAT program, office-based MAT, or bridge clinic) within 14 days following hospital discharge. Engagement is defined as having two encounters in an outpatient MAT program or, for office-based treatment, filling two prescriptions for buprenorphine or naltrexone, or receiving one prescription that covers at least 28 of the first 30 days following treatment initiation. MAT programs are outpatient addiction treatment programs that provide methadone and/or buprenorphine maintenance treatment.

Outcome measures are mainly assessed using administrative data from Medicaid claims, the H+H clinical data warehouse, and DOHMH overdose data. These data sources are further detailed in Section 3.1. *Medicaid claims* as the primary data source. Medicaid claims have data from each visit to a MAT program, and for filled prescriptions (including # of days of treatment prescribed). The supplemental data source is the H+H clinical data warehouse, which can be used to identify patients who are *not* covered by Medicaid (incl. Medicare and uninsured) who had an OUD diagnosis or received MAT during the hospital stay. The *H+H clinical data warehouse* is a secondary data sources, and captures all patients who receive addiction treatment within the H+H treatment system.

**Table 1. Outcome measures by specific aim**

| Specific Aim                                      | Definition                                                                                            | Primary Data Source
(Secondary Data Source)   |
|---------------------------------------------------|-------------------------------------------------------------------------------------------------------|--------------------------------------------------|
| Aim 1: Treatment initiation and engagement |                                                                                                       |                                                  |
| Treatment initiation                              | Outpatient MAT encounter w/in 14 days of hospital discharge
(def. MAT program or office-based MAT) | Medicaid claims
(H+H clinical data warehouse) |
| Treatment engagement                              | Receipt of 2+ additional MAT services w/in 30                                                         | Medicaid claims                                  |

|                                                    |                                                                                                                   |                                                                     |
|----------------------------------------------------|-------------------------------------------------------------------------------------------------------------------|---------------------------------------------------------------------|
|                                                    | days of initiation
(def. MAT program encounters or prescriptions for MAT)                                      | (H+H clinical data warehouse)                                       |
| Aim 2: Treatment retention                  |                                                                                                                   |                                                                     |
| Rate of treatment retention                        | Continuous retention in treatment for 6 months
(def. MAT program visits and/or MAT Rx for $\geq 80\%$ of days) | Medicaid claims
(H+H clinical data warehouse)                    |
| Aim 3: Acute care utilization and OD deaths |                                                                                                                   |                                                                     |
| Acute care                                         | Hospital and ED admissions in 6 months and 12 months following discharge                                          | Medicaid claims
(H+H clinical data warehouse)                    |
| OD death                                           | Poisoning death involving opioid(s)                                                                               | DOHMH overdose data
(Medicaid claims)                            |
| Aim 4: Implementation outcomes              |                                                                                                                   |                                                                     |
| Reach                                              | Received any CATCH service(s)                                                                                     | H+H clinical data warehouse                                         |
| Adoption                                           | Referrals made to the CATCH by clinical staff                                                                     | H+H clinical data warehouse                                         |
| Implementation fidelity                            | Ability to reach target population and deliver MAT; barriers and facilitators                                     | Interviews w/ CATCH staff and patients with OUD; CATCH program data |

Qualitative interviews to assess implementation outcomes (Aim 4), will explore organizational (organizational readiness, culture, priorities), individual (attitudes, norms), and intervention characteristics (complexity, relative advantage), as defined by the Consolidated Framework for Implementation Science (CFIR). CFIR will guide qualitative interviews with staff and patients at baseline and post intervention. Interview guides will include COVID-19-related questions to gather information for our qualitative analysis on how the pandemic affected treatment access and care of patients as well as the services offered by CATCH hospital staff members.

The economic analysis will incorporate both acute and ambulatory care costs to assess the economic impact of the CATCH intervention. The CATCH intervention could reveal significant implications for broader health economic outcomes, such as patients' health-related quality of life and changes in non-healthcare resource usage (e.g., unemployment expenses) post-discharge. Although quality of life and non-healthcare resources are not collected directly from CATCH participants, we will estimate these using published literature (e.g., health-related quality of life) and public data sources (NY state unemployment statistics) within an economic evaluation simulation model. Acute care utilization measures are specified in Table 1. Additional measures of ambulatory care and SUD treatment utilization are captured in Medicaid claims data, and measured for 6 and 12 months following hospital discharge, and include:

- Outpatient medical visits, including primary care, psychiatry, and other ambulatory medical care
- SUD treatment program visits, including to outpatient and residential treatment programs

The CATCH service sees patients with other substance use disorders (SUD) in addition to OUD. Therefore, as part of our evaluation, we will be collecting descriptive data on patients with alcohol use disorder (AUD) and other SUDs; we will also explore similar aims to our OUD aims (Aims 1-4) with these populations. Exploratory measures for AUD treatment and outcomes are collected from chart review and include:

- Orders for medications to treat AUD during hospitalization
- Prescriptions for medications to treat AUD medications
- Emergency department and primary care visits

Procedures for the AUD chart reviews are described in Section 3.1.

## 1.8. Power calculation and sample size

Study outcomes are assessed using administrative data and applying the case definition specified in Section 2.3. We anticipate that approximately 9,000 cases (4,500 in the treatment as usual period, 4,500 in the intervention period) will qualify for inclusion in the analysis. Simulations were used to assess the statistical power to detect a range of effect sizes

for the probability of initiation over a 12-month period. Based on pilot data from Medicaid claims, we expect that 7% of the individuals under treatment as usual (TAU) will initiate MAT (range is 4-9%). We wish to be able to detect an increase in the initiation rate of 15 to 25 percentage points, and pilot data indicates that this is attainable. We conservatively assume that the variance of the cluster-level random effect on the logistic scale is approximately 0.16, which is equivalent to an ICC of 0.05. In the absence of pilot data to estimate the ICC, 0.05 is a large and therefore conservative assumption; the true ICC is likely smaller, and thus our proposed design should yield even higher statistical power.

In simulations, 1000 iterations were used to estimate the power. For each iteration, a generalized linear mixed model was fit to randomly generated data and p-values were assessed to determine if the effect was detected. With six sites of at least 700

| Table 2 |      | CATCH rate |      |     |      |     |      |
|----------------|------|------------|------|-----|------|-----|------|
| POWER N > 700  |      | 0.20       | 0.25 | 0.3 | 0.35 | 0.4 | 0.45 |
| TAU rate       | 0.05 | 95%        | 99%  | 99% | 99%  | 99% | 99%  |
|                | 0.1  | 57%        | 80%  | 96% | 98%  | 99% | 99%  |
|                | 0.15 | 21%        | 48%  | 67% | 89%  | 97% | 99%  |

patients per site, we have power to detect these effects using a two-sided, 0.05-level test. Specifically, we have 80%, 95%, and 99% power to detect effect sizes of 0.13, 0.18, and 0.23, respectively; these effect sizes translate to a treatment initiation rate in the intervention group of 20%, 25%, and 30%, respectively. Table 2 shows power for a range of initiation rates in the TAU period and the CATCH period; the proposed sample size yields adequate power for nearly every combination.

Up to 120 individuals (60 staff, 60 patients) will be enrolled in the study, and will participate in qualitative interviews as described below.

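### The power figures in protocol section 1.8 do not follow from the stepped wedge in section 1.4; on the stated inputs they understate power, and the ICC reassurance carries little weight

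*Protocol*

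**What the plan says.** Section 1.4 describes a stepped wedge over 14 quarters: "Each of the 6 participating hospitals will be randomly assigned to one of 6 start times", with start times about three months apart. Every hospital is observed under both usual care (TAU) and CATCH.

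Section 1.8 reports power from 1,000 simulated data sets, each analysed with a generalized linear mixed model, "using a two-sided, 0.05-level test". The expected TAU initiation rate is 7% (range 4-9%). It gives one variance component: "the variance of the cluster-level random effect on the logistic scale is approximately 0.16, which is equivalent to an ICC of 0.05". For six sites with at least 700 patients each it concludes that "we have 80%, 95%, and 99% power to detect effect sizes of 0.13, 0.18, and 0.23, respectively", which it equates with "a treatment initiation rate in the intervention group of 20%, 25%, and 30%, respectively". Table 2 gives 18 further values for TAU rates of 5%, 10% and 15%, and the text says that "the proposed sample size yields adequate power for nearly every combination". On the ICC it says that "0.05 is a large and therefore conservative assumption; the true ICC is likely smaller", and infers that power should be higher still. The section does not mention steps, period effects, or any variance component beyond the site intercept.

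**The concern.** In a stepped wedge each hospital serves largely as its own control, so most of the site intercept cancels from the treatment contrast. Several power values in section 1.8 are far lower than such a design should give with 700 patients per site. The argument that a large ICC is the cautious choice is also one that matters mainly when whole hospitals are compared with each other.

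At stake is whether the power statement for the primary aim describes this trial. If it describes another design or another sample size, a reader cannot tell how much margin the trial has, or which assumptions that margin depends on.

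**Working it through.** **Inputs from the protocol.** Section 1.8: six sites, N = 700 per site, site-intercept variance 0.16 on the logit scale, two-sided alpha 0.05, the stated rates. Section 1.4: six start times, 14 quarters.

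**Assumptions added here.** One hospital crosses over at the start of each of quarters 5 to 10, each site has N/14 = 50 patients per quarter, quarter effects are fixed, the secular trend is flat, and there is no random effect beyond the site intercept.

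**ICC conversion.** 0.16/(0.16 + π²/3) = 0.16/(0.16 + 3.29) = 0.046, which agrees with the stated 0.05.

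**Standard error implied by the stated power.** SE = log odds ratio/(z_power + 1.96). For 7% versus 20% the log odds ratio is 1.200, so 80% power implies 1.200/(0.842 + 1.96) = 0.428. For 10% versus 20%: 0.811/(0.176 + 1.96) = 0.380.

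**Standard error of the wedge.** Generalized least squares on the 6 × 14 cell log-odds. Each cell has sampling variance 1/[n p(1−p)] with n = 50, cells in the same site share covariance 0.16, and the fixed effects are 14 quarters plus treatment. Power = Φ(log odds ratio/SE − 1.96). For 7% versus 20%: 1.200/0.208 − 1.96 = 3.81, so power is about 100%. For 10% versus 20%: 0.811/0.190 − 1.96 = 2.31, so 99%.

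| TAU vs CATCH | Log odds ratio | Implied SE | Wedge SE | Stated power | Wedge power |
|---|---|---|---|---|---|
| 7% vs 20% | 1.200 | 0.428 | 0.208 | 80% | about 100% |
| 7% vs 25% | 1.488 | 0.413 | 0.201 | 95% | about 100% |
| 7% vs 30% | 1.739 | 0.406 | 0.197 | 99% | about 100% |
| 10% vs 20% | 0.811 | 0.380 | 0.190 | 57% | 99% |
| 15% vs 20% | 0.348 | 0.302 | 0.173 | 21% | 52% |
| 15% vs 25% | 0.636 | 0.333 | 0.167 | 48% | 97% |
| 15% vs 30% | 0.887 | 0.370 | 0.163 | 67% | about 100% |

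Simulated logistic mixed models with quarter effects agree: 51.7% for 15% versus 20%, 98.5% for 15% versus 25%, 99.8% for 10% versus 20% and 100% for 7% versus 20%. Simulation noise in the plan's own figures is too small to explain the gaps: at 57% with 1,000 runs the 95% margin is 1.96 × √(0.57 × 0.43/1000), about 3 points.

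**Variants.** Leaving out quarter effects raises power further (98% for 15% versus 20%). So does using 1,500 per site, which is 9,000/6 (83% for 15% versus 20%). Restricting each site to 12 months either side of crossover, still with 700 per site, gives 56%, 98% and 99.5% for 15% versus 20%, 15% versus 25% and 10% versus 20%. No variant tried came within 2 points of Table 2 throughout. Two came closer than the rest:

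- A parallel comparison of three hospitals with three others, 700 each, gives 18/47/75/91/98% in the first five cells of the 15% row (stated 21/48/67/89/97%). It gives 67% for 10% versus 20% (stated 57%) and 94% for 7% versus 20% (stated 80%).
- A wedge with about 150 patients per site gives 78/94/99% for the three 7% contrasts, with a largest gap of 6 points in Table 2.

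**Role of the ICC in the wedge** (15% versus 20%, 700 per site):

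| ICC | Power |
|---|---|
| 0 | 61% |
| 0.01 | 54% |
| 0.05 | 52% |
| 0.10 | 52% |
| 0.20 | 51% |

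For 7% versus 20% the SE moves only from 0.203 at ICC 0.01 to 0.208 at 0.05. In a parallel three-versus-three trial (10% versus 20%), power falls from 94% at ICC 0.02 to 64% at 0.05 and 37% at 0.10.

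**Components the section does not state (values assumed).** A between-site treatment-effect variance of 0.16 leaves 99.5% power for 7% versus 20%, but 31% for 15% versus 20%. For 7% versus 20%, a treatment-effect variance of 0.5 leaves 92%, and a site-by-quarter variance of 0.30 leaves 96%.

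**The case against.** The best defence is that the error is on the safe side. Understated power leaves slack, and even with large assumed extra variances power for 7% versus 20% stays at 92-96%, above the stated 80%. Cases come retrospectively from administrative data, so re-running the simulation changes no recruitment target. This stands, and it limits the point to a correction of the power statement.

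Stronger readings are tempting, but the protocol does not support them:

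- **That an ICC of 0.05 is anti-conservative.** It is not. On the protocol's logit scale the wedge SE rises slightly with the ICC, so 0.05 is weakly conservative. With total variance held fixed instead (linear model), the least favourable ICC is about 0.02, at 52.8% against 53.6% for 0.05, a gap of under 1 point.
- **That Table 2 was computed for three hospitals against three.** A wedge with about 150 patients per site fits about as well, and the text does not settle which, if either, was simulated.
- **That the final test will have an inflated error rate.** That depends on the random-effects structure and small-sample method of the final analysis, which section 3.3.a leaves to the SAP, not available here.
- **That 700 per site contradicts the 9,000 cases.** The text says at least 700, and 1,500 per site satisfies that. So does 4,500/6 = 750 per site and condition. The meaning is unclear, but there is no contradiction.
- **That the claim of adequate power for nearly every combination is false.** Four of 18 cells are below 80% (57, 21, 48, 67), but all have a TAU rate of 10% or 15%, above the expected 4-9%. The wording is generous and no more.

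The crossover quarters are also an assumption, since the shading of Figure 1 is not available. The variants above show that the gap does not depend on the exact layout.

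**Conclusion.** The stated power is wrong as a description of this trial. With the inputs of section 1.8 and the design of section 1.4, the 80/95/99% become about 100% each, and the Table 2 cells checked at 57%, 48%, 67% and 21% become 99%, 97%, about 100% and 52%. The implied standard errors are roughly twice those of the wedge (for example 0.428 against 0.208). This rests on crossover at quarters 5 to 10, equal quarterly cells, fixed quarter effects and a random intercept only.

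A reader might infer that the trial is too small. The calculation shows the opposite under the stated model: power for the target effect is understated. The ICC sentence is right in direction but gives almost no reassurance, because the quantity it discusses hardly affects a wedge. The components that could reduce power, site-by-period variation and differences between hospitals in the CATCH effect, are not stated in section 1.8.

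**What to change.** In section 1.8:

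1. Re-run the simulation for the actual design: six sequences, quarter effects, and expected cases per site and quarter.
2. Say whether 700 is per site or per site and condition, and how it relates to the 9,000 anticipated cases.
3. Replace Table 2 and the 80/95/99% sentence with the new results.
4. Replace the ICC reassurance with power over a stated range of site-by-period variances and between-site treatment-effect variances.

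The cost is a few hours of simulation and a rewritten paragraph. The restated power may look less favourable under the larger variances. No more patients are needed.
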